**Figure 3 F3:**
[figure not shown]
Online training learning modules for implementation of BCP-VAMOS, version 3.0. Brazil. Adapted from Konrad et al. (21).

**Table 1 T1:** Description of strategies for groups with and without ongoing support for the implementation of BCP-VAMOS, version 3.0. Brazil.

**Intervention stage**	**Traditional didactic approach group^a^**	**Consultee-centered training + action planning approach group^b^**
**Program dissemination, participants enrollment**	Printed material to publicize and recruit the community: posters, flyers, and business cards.	Printed material plus guidelines to optimize dissemination and recruitment: who, where, when, and how.
**Program sections** (18 sections)	T-shirt with program logo for the provider. Digital guidelines, printed material to conduct the sections, record the frequency, and monitor and evaluate the sections.	T-shirt, manual, printed material plus guidelines for each of the sections: preparation of the site, reception, content guiding, participation registration, and individual section monitoring.
**Participants evaluation** (baseline and post-intervention)	Digital guidelines, video, and printed material to record the participants' baseline and post-intervention assessment data.	Digital guidelines, video, printed material plus guidelines for carrying out evaluations about: location, professionals involved, and the necessary care for reliable measures.

^a^20-h online training (21) + teaching materials. ^b^20-h online training (21)+ teaching materials + structured messages throughout the implementation process.

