This group will participate in the 20-h online training as described above and will receive ongoing support centered on the provider, using an action planning strategy. Ongoing support (see Table 1) will be structured by a specialist PHC researcher and provided during 12 months for all the implementation stages: recruiting the community, conducting program sessions, and evaluating participants. Support will focus on the process of identifying barriers to program implementation, selecting strategies to deal with barriers and goals for recruiting and retaining new participants. Before the start of each stage, the intervention provider will receive a message reinforcing the strategy that should be used. After each stage, another contact will be made to assess the used strategy and provide new feedback. Support will be delivered through interviews with the provider using a smartphone messaging app.

Both groups will be monitored simultaneously. If the CG providers have questions during the implementation process, these will be answered at their origin, but, being careful not to offer strategies similar like those IG will be offered. Thus, both groups will be monitored by one single researcher to avoid communication bias and to ensure that information from the IG is not passed on to the CG. This researcher will be a specialist in the health area, particularly in PHC, and received training to implement the BCP-VAMOS.

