### New description

The randomization and allocation of health professionals into the two groups (CCT + APA vs. TDA) will be performed after all PHC professionals complete the online training. Through a randomly generated computer sequence, we will randomize each facility to one of the intervention arms with all eligible professionals within each facility randomized to the same intervention arm to avoid cross-contamination within the same facility. However, multiple facilities within the same city may be randomized to different groups. After randomization, they will be asked to implement BCP-VAMOS in their workplaces. The randomization and assignment of groups will be under the responsibility of a single researcher and will be blind to the others involved in the implementation strategies and data collection.

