**Effectiveness**, assessed at the individual level, refers to the extent of the intervention's impact on the primary outcomes, how it changes behavior and affects the quality of life, and whether or not there are unintended results (positive or negative) (22). In this study, effectiveness will be assessed considering the primary outcomes of BCP-VAMOS: physical activity and eating behavior. Physical activity will be assessed through a self-report of the weekly practice (type, frequency, and duration) (34) and by accelerometry (35), which allows measuring the time spent on sedentary behavior, light, moderate, and vigorous physical activity. Eating behavior will be assessed through the habit and frequency of consumption of foods classified as healthy (fruits, greens, and raw or cooked vegetables) and unhealthy (sweets, snacks, and sugary drinks) (34). These data will be collected by the PHC professionals through a validated questionnaire for the BMC-VAMOS program (33). The effectiveness outcomes will be analyzed by PHC professional (staff level) to assess the impact of intervention strategies, comparing the IG to the CG.

**Adoption** is a measure at the organizational level of participation that refers to the representativeness of locations and/or agents who are willing to implement an intervention, considering those who are eligible (22). In this study, the number, proportion, and representativeness of local/PHC professionals who initiate the program delivery will be calculated using those certified by the online training with eligibility criteria. We will calculated the adoption rate by considering the ratio between the number of PHC professionals who initiated the implementation of the program in each UBS and the number of PHC professionals certified by the online training, multiplied by 100. To identify the factors that will influence the program adoption and non-adoption, qualitative data will be collected through interviews with PHC professionals.

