### Data collection

The BCP-VAMOS implementation process will be monitored for 12 months. The data will be collected through electronic forms, a smartphone messaging application, observations, and semi-structured interviews with key informants involved in the implementation strategies. The interviews will be conducted by phone or in-person by an independent co-investigator who will not participate in the other stages of the study. The variables referring to BCP-VAMOS participants will be collected by the health professionals responsible for implementation at the baseline and during post-intervention. This information will be recorded and shared with the research team using electronic spreadsheets. A trained researcher will collect accelerometry data *in loco*. The instruments for collecting data in each stage of the study will be developed based on recent recommendations for pragmatic studies (28), the RE-AIM checklist (37), the CFIR matrices (www.cfirguide.org), and the questionnaire for effectiveness evaluation, designed for the BCP-VAMOS (33). Participants' consent will be collected by health professionals before the intervention starts. We will train independent research to evaluate the process. All data regarding the implementation of BCP-VAMOS will be managed by one single researcher to maintain data quality and reliability. The confidentiality of the participant is guaranteed using identification code numbers to match the treatment data in the computer files for each group.

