### Data analysis

Quantitative data will be expressed through descriptive analysis (absolute and relative frequency, mean and standard deviation) and inferential analysis to compare the impact of the intervention between the groups. To compare the characteristics between the groups, Fischer's exact and chi-square tests will be used. To verify the effect of the intervention, Student's paired t test or Wilcoxon test (continuous variables) and McNemar test (categorical variables) will be used. To compare changes between groups, Student's t test or Mann-Whitney *U*-test will be applied. The analyses will be performed using a 5% probability, and will be generated using the Statistical Package for the Social Sciences (SPSS)^®^ software, version 22.0. Qualitative data will be fully transcribed by a researcher, and their quality will be assessed by a second researcher. Through the technique of descriptive content analysis (38), the texts will be pre-analyzed (each interview will be read), coded (reduced to units of meaning consistent with the purpose of the study), and categorized (the participants' answers will be organized). The information will be coded deductively, following the conceptual model of the study and, if necessary, inductive codes will be added until saturation is achieved (39). The data will be double-coded in the QSR NVivo^®^ 12.0 software by two trained researchers. Intercoder reliability will be assessed employing Cohen's kappa (criterion> 0.80).

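### Guidance on taking reliable outcome measurements goes to the intervention arm only, and the supported providers collect their own participants' questionnaire outcomes, so part of a between-arm difference may be measurement

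*Protocol article*

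**What the plan says.** All references are to the protocol article.

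- **Table 1, participant evaluation row (baseline and post-intervention).** The control entry reads "Digital guidelines, video, and printed material to record the participants' baseline and post-intervention assessment data". The intervention entry lists the same kinds of material, then adds "plus guidelines for carrying out evaluations about: location, professionals involved, and the necessary care for reliable measures".
- **Description of the study design.** Both arms take the same 20-hour online training, which covers the program's evaluation forms. Ongoing support, for the intervention arm only, covers three stages: "recruiting the community, conducting program sessions, and evaluating participants". It is timed to each stage: "Before the start of each stage, the intervention provider will receive a message reinforcing the strategy that should be used". A further contact after the stage gives feedback. Control providers may ask questions, but the answers must avoid strategies like those given to the intervention arm.
- **Data collection.** "The variables referring to BCP-VAMOS participants will be collected by the health professionals responsible for implementation at the baseline and during post-intervention". A trained researcher takes the accelerometry.
- **Outcomes evaluation, Effectiveness paragraph, and Table 2.** The primary outcomes are physical activity (self-report and accelerometry) and eating behavior. Providers use a validated questionnaire. Results are analyzed by professional, intervention against control. Table 2 expresses effectiveness as the proportion of participants whose behavior changed, and its footnote says providers collect these data.
- **Randomization and New description.** Group assignment "will be blind to the others involved in the implementation strategies and data collection".

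**The concern.** The trial asks whether ongoing support improves results over didactic training alone. For that comparison, the outcome should be measured in the same way in both arms. Here the support includes advice on how to take the measurement, that advice is deliberately kept from the control arm, and those who receive it are the assessors. If advised providers question participants differently, recorded activity or diet can differ between arms even when behavior does not. No between-arm test on questionnaire data alone can separate the two explanations.

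The blinding statement would reassure a reader on this point, but it cannot be true of intervention providers. They receive the support messages and they collect the data.

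**Working it through.** **1. The measurement process, arm by arm**

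| Element | Control | Intervention |
|---|---|---|
| 20-hour training, including evaluation forms | yes | yes |
| Digital guidelines, video, printed material | yes | yes |
| Extra guidance on setting, staff and reliability of measures | not listed | yes |
| Message before and feedback after the evaluation stage | no | yes |
| Who administers the questionnaire | delivering provider | delivering provider |
| Who takes accelerometry | trained researcher | trained researcher |

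The arms differ in rows three and four only. Those rows bear on the questionnaire and not on accelerometry.

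**2. When it biases a change score**

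Let *d0* and *d1* be the arm difference in measurement shift at baseline and post-intervention. Then

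observed difference in mean change = true difference + (*d1* − *d0*).

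If *d1* = *d0*, the shift cancels. The article gives no assurance of that, because feedback follows each stage and intervention practice may change between the two visits. Baseline is not a clean reference either: providers are randomized before they implement the program, so their baseline assessments follow allocation.

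**3. Illustrative size**

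The only size figure in the article reproduces: 45 professionals × 8 participants = 360. I assume an equal split, 180 per arm, no true effect and a two-sided 5% z-test. The article gives no measurement-error figure, so *b* = *d1* − *d0* (in SDs of change) is assumed.

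SE = √(2 × DE / 180), and rejection rate = 1 − Φ(1.96 − *b*/SE) + Φ(−1.96 − *b*/SE).

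- DE = 1 (no clustering): SE = 0.105.
- DE = 1 + (8 − 1) × 0.05 = 1.35 (assumed ICC 0.05, groups of 8, clustering allowed for in the test): SE = 0.122.

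| *b* (SD) | DE = 1 | DE = 1.35 |
|---|---|---|
| 0 | 5% | 5% |
| 0.1 | 16% | 13% |
| 0.2 | 48% | 37% |
| 0.3 | 81% | 69% |

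**4. Proportion showing change (the Table 2 metric)**

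Assume that 30% truly change in both arms. Observed proportion = sensitivity × 0.30 + (1 − specificity) × 0.70.

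- Intervention 0.9/0.9: 0.27 + 0.07 = 34%. Control 0.8/0.8: 0.24 + 0.14 = 38%. Spurious difference −4 points, rejected about 12% of the time (180 per arm, no clustering).
- Intervention 0.9/0.8: 0.27 + 0.14 = 41%. Control 0.9/0.9: 34%. Spurious difference +7 points, rejected about 28% of the time.

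**5. If the guidance only reduces random error**

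Mean change stays unbiased, but a thresholded proportion can still move. Assume true change ~ N(0.3, 1), with error variance 0.25 in the intervention arm and 1.0 in control.

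- Threshold 1.0: 1 − Φ(0.7/√1.25) = 26.6% against 1 − Φ(0.7/√2) = 31.0%, a difference of about −4.5 points (from unrounded values).
- Threshold 0: Φ(0.3/√1.25) = 60.6% against Φ(0.3/√2) = 58.4%, a difference of +2.2 points.

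The sign depends on the assumptions, so the direction cannot be read from the article.

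**The case against.** The strongest reply is that control providers are well prepared. They pass the same training with at least 80% in the final quiz, receive guidelines and a video for the assessments, may ask questions, and use the same validated questionnaire. This stands. A reader might infer that only one arm is trained to measure; the article does not support that. The documented difference is an added layer of guidance and messages.

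Second, guidance aimed at reliability may only reduce noise, and it applies at both visits, so a constant shift would cancel in change scores. This also stands as a limit on the claim. It does not remove the risk, because equal shifts are not assured and the Table 2 proportion can move even under pure noise.

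Third, physical activity has an objective component, described as "by accelerometry (35), which allows measuring the time spent on sedentary behavior, light, moderate, and vigorous physical activity" and collected by a researcher. This confines the point to the questionnaire outcomes, which include all of eating behavior.

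Fourth, evaluating participants is one of the three supported stages, so coaching on it belongs to the strategy under test. That is a fair description of the design. But where the coached activity produces the trial's own outcome data, the comparison of those data is compromised.

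A reader might also count the listed activity and food components and, from "The analyses will be performed using a 5% probability", infer a large multiplicity problem. The article does not state how many measures are tested as primary, and such choices are commonly left to an analysis plan, so that inference is not made here.

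**Conclusion.** The point holds for self-reported physical activity and eating behavior. As written, the randomized strategy includes measurement guidance withheld from control, and those who receive it assess their own participants, so a between-arm difference may partly reflect measurement. A reader might go further and conclude that measurement error does differ by arm, or that all primary outcomes are biased. The article supports neither: it shows a route, not an amount or a sign, and accelerometry lies outside that route.

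The size is unknown. The 13–16% error rate at 0.1 SD and the −4 to +7 points from misclassification are illustrations under assumed errors, an equal split of 360 and, where stated, an ICC of 0.05.

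Separately, the blinding statement in Randomization and New description contradicts the description of support and the Data collection section as far as intervention providers are concerned. Whether control providers are told their arm is not stated.

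**What to change.** 1. In the participant evaluation row of Table 1, move the guidance on setting, staff and reliable measurement into the materials common to both arms, and send any message about measurement practice to both. Keep recruitment and program-delivery support as the contrast.
2. In Randomization and New description, say that the providers who collect questionnaire data are not blind to assignment, and limit the blinding claim to those for whom it can hold.
3. State that between-arm results for the questionnaire outcomes will be interpreted alongside the researcher-collected accelerometry.

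**Cost.** The guidance already exists, so the work is distributing it, editing the text and registering the change in ReBEC, as the Study design section requires. The downside is that evaluation coaching is no longer part of the tested strategy. Providers would still assess their own participants, so some assessor risk remains. Independent questionnaire assessors would reduce it further, but at greater cost.

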### Recruitment and eligibility

The online training will be disclosed to PHC professionals electronically and the enrolment will be performed on the BCP-VAMOS website (vamos.ufsc.br). The training will be available during 4 months for qualification and certification of health professionals. When the PHC professionals are enrolled in the online training, they will be informed about the research objectives and procedures. Their participation will be accepted after they sign the Free and Informed Consent Form.

#### Inclusion criteria

The PHC professional must have a college degree, work in PHC, and be authorized by the manager of the municipal health department to implement the BCP-VAMOS.

#### Exclusion criteria

Those enrolled PHC professionals who do not complete the online training will be excluded from the study.

### Randomization

The randomization and allocation of health professionals into the two groups (CCT + APA vs. TDA) will follow a sequence randomly generated by a computer. This process will be carried out after all the PHC professionals complete the online training. Health professionals from the same workplace will be assigned to the same group should more than one professional participate in the online training. After randomization, they will be asked to implement the BCP-VAMOS in their workplaces. Randomization and group assignment will be under the responsibility of one single researcher and will be blinded to the others involved in the implementation strategies and data collection.

### New description

The randomization and allocation of health professionals into the two groups (CCT + APA vs. TDA) will be performed after all PHC professionals complete the online training. Through a randomly generated computer sequence, we will randomize each facility to one of the intervention arms with all eligible professionals within each facility randomized to the same intervention arm to avoid cross-contamination within the same facility. However, multiple facilities within the same city may be randomized to different groups. After randomization, they will be asked to implement BCP-VAMOS in their workplaces. The randomization and assignment of groups will be under the responsibility of a single researcher and will be blind to the others involved in the implementation strategies and data collection.

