### Study location and participants

The study will be conducted with professionals from health teams that work in PHC in the state of Santa Catarina, southern Brazil. The state has 295 municipalities and an estimated population of 7,250,000 inhabitants. It is the third state in the national human development index (HDI = 0.774), has the lowest social inequality index (GINI = 0.494) and the highest performance index of the unique health system in the country (IDSUS = 6–6.99). PHC in Santa Catarina is divided into seven regions, with 1,824 primary care centers, 1,855 family health teams, 234 primary care teams (doctor, nurse, dentist), and 301 multidisciplinary teams (nutritionist, pharmacist, physiotherapist, physical education professional, psychologist, social worker). These teams take into consideration the multi-professional health care policy and are formed by 7,056 PHC professionals with bachelor's degree (30). As the VAMOS program in the face-to-face version requires a minimum of 8 people to start a group and we expect that around 45 health professionals can complete the training, a total of at least 360 adults may be recruited to participate in the program.

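### With about 45 or fewer facilities expected, all known before a single batch allocation, the article states no restriction on the randomization and only unadjusted between-group tests, leaving a sizeable chance of facility-level imbalance

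*Protocol article*

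**What the plan says.** The protocol article describes allocation twice, under Randomization and again under New description. The second account makes the facility the unit: "Through a randomly generated computer sequence, we will randomize each facility to one of the intervention arms". Colleagues at one workplace are kept together by a separate rule, which has "all eligible professionals within each facility randomized to the same intervention arm". Allocation "will be performed after all PHC professionals complete the online training", and the Exclusion criteria settle who is on the list by then: "Those enrolled PHC professionals who do not complete the online training will be excluded from the study".

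The two accounts cover timing, unit, the rule for colleagues at one workplace, facilities in the same city, the person responsible and blinding. Neither mentions an allocation ratio, stratification, blocking, matching, minimization or a balance constraint.

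On numbers, Study location and participants states: "we expect that around 45 health professionals can complete the training". The program "requires a minimum of 8 people to start a group", from which "a total of at least 360 adults may be recruited to participate in the program". No number of facilities is given. The same section describes a varied setting, with several kinds of health team, and notes that "PHC in Santa Catarina is divided into seven regions".

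Data analysis compares changes between groups by Student's t test or the Mann-Whitney U-test. It names no covariate adjustment.

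**The concern.** With a few dozen randomized units, chance alone can leave the arms visibly different on facility characteristics that may bear on recruitment, retention and delivery. Restricted randomization is the usual protection. The usual obstacle to it, units arriving one at a time, is absent here because the whole list exists before anyone is allocated. The named tests would not correct for an imbalance that arose.

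Precision and credibility are at stake. If, for example, most multi-professional facilities fell in the ongoing-support arm, a difference in reach or effectiveness would be hard to attribute to the support, even though the randomization itself was valid.

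**Working it through.** **Inputs from the article.** About 45 professionals are expected; the minimum group size is 8; the facility is the unit; there is one allocation after training; no restriction is stated; the tests are unadjusted.

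**The plan's own figure.** 45 × 8 = 360, which matches the stated minimum number of adults. This counts one group per professional. It does not give the number of facilities.

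**Assumptions, because the article gives no figures.** The number of facilities m is 45 if every professional works at a different facility, and fewer otherwise; 30 is the main lower case and 20 an extreme one. A facility trait is held by half of the facilities. Unrestricted allocation means an independent 50:50 draw for each facility.

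**1. Arm sizes.** The number in one arm is Binomial(m, 0.5).
- m = 45: 2 × P(X ≥ 27) = 0.233 for a 27:18 split or worse.
- m = 30: 2 × P(X ≥ 18) = 0.362 for an 18:12 split or worse.

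Efficiency relative to equal arms is n₁n₂/(m/2)². For 27:18 this is 486/506.25 = 0.96, and for 18:12 it is 216/225 = 0.96. Unequal arms at this level therefore cost about 4%.

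**2. A binary facility trait.** Given arm size n, the number of trait facilities in that arm is hypergeometric; this is averaged over the binomial for n. Probability of a difference of at least the stated size:

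| Facilities | 20 points or more | 30 points or more |
|---|---|---|
| 45 | 21.0% | 4.0% |
| 30 | 36.2% | 11.2% |
| 20 | 50.3% | 26.8% |

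Forcing equal arms and nothing else does not settle the matter: the 20-point probability becomes 13.9% at 45 and 46.6% at 30. The rise at 30 comes from discreteness, since with 15 per arm and 15 trait facilities a 9:6 split is exactly 20 points.

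**3. Continuous facility covariates, equal arms.** The standardized mean difference (SMD) has standard deviation √(4/m): 0.298 at 45 and 0.365 at 30. For one covariate, P(|SMD| > 0.5) is 9% and 17% respectively.

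**4. Effect of constraining.** This was simulated with four independent covariates (three continuous, one binary), 200 covariate sets and 4,000 equal splits each, keeping the best-balanced 10%. Chance that at least one covariate exceeds the threshold:

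| Facilities | SMD > 0.5, equal split only | SMD > 0.5, constrained | SMD > 0.25, equal split only | SMD > 0.25, constrained |
|---|---|---|---|---|
| 45 | 32% | 0% | 87% | 10% |
| 30 | 56% | 0% | 95% | 52% |
| 20 | 73% | 0.02% | 97% | 68% |

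Even with 20 facilities there are C(20,10) = 184,756 equal splits to choose from.

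**5. Region, for illustration only.** If facilities were spread nearly evenly over all seven regions, the chance that at least one region falls wholly in one arm is 1 − ∏(1 − 2 × 0.5^k), where k is the number of facilities in a region. With 45 facilities (three regions of 7, four of 6): 1 − 0.984375³ × 0.96875⁴ = 0.160. With 30 (two of 5, five of 4): 1 − 0.9375² × 0.875⁵ = 0.549. The article does not give the spread.

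**The case against.** The strongest reply is that unrestricted allocation is inferred from silence. A blocked or constrained list is also a computer-generated sequence, and a journal article may leave such details to the full protocol. This stands as a caution, which is why the figures above are conditional. It does not dispose of the point: the article spends two paragraphs on allocation, down to facilities in the same city, and states no restriction in either. It also names its between-group tests, and they are unadjusted.

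Several stronger inferences are tempting and should not be drawn.
- **That facilities cannot exceed 45.** The article gives an expectation, not a cap.
- **That the facilities span all seven regions and differ in number of professionals.** The regions describe the state, and the workplace rule under Randomization is conditional on colleagues taking part. Both are assumptions. Workplace is plausibly known at enrolment; facility size and staffing are not shown to be known before allocation.
- **That the comparison is biased, or that imbalance could match the effect of support.** Chance imbalance does not bias a randomized comparison on average. The article states no expected effect and no link between facility traits and outcome, so its size against the support effect cannot be judged.
- **That restriction would remove imbalance at no cost.** Smaller differences remain, unmeasured factors are untouched, and professionals start the program only after allocation, so balance among those who actually deliver it is not secured.

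Stratified blocks also have limits: seven regions by two size classes is 14 strata, or 45/14 ≈ 3.2 and 30/14 ≈ 2.1 facilities each, so many blocks would be incomplete. That favors constrained randomization over fine stratification.

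**Conclusion.** The point holds as an improvement worth making, not as an error that invalidates the design. On the natural reading of the article, a facility trait with 50% prevalence has a 21% (45 facilities) to 36% (30 facilities) chance of differing by 20 points or more between arms, and the stated tests would leave that uncorrected. Covariate imbalance is the harm that matters; unequal arm sizes cost only about 4% of efficiency at 27:18.

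The conclusion rests on three assumptions: allocation is unrestricted, the facilities number about 30 to 45, and the traits in question bear on the outcomes. If a restriction is already planned, stating it, with matching adjustment in the analysis, resolves the point.

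**What to change.** Under New description, state that facilities will be randomized 1:1 in one batch by covariate-constrained randomization. Constrain on a few facility factors known at enrolment, for example region (grouped if sparse) and number of certified professionals per facility if this varies. Fix the factors and the balance criterion before allocation. In Data analysis, include the same factors in the between-arm comparison in place of the unadjusted test alone.

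The cost is a short script at the allocation step, a sentence in each section, and confirmation that the facility data are in hand before allocation. The adjusted analysis loses a few degrees of freedom: ungrouped region (6) plus a two-level professional count (1) would use 7, which is a reason to group regions. No extra participants or recruitment time are needed.
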